### Data collection and statistical analysis

Data will be collected from participants via daily face-to-face and telephone interviews and recorded in the CRFThe statistical package, Epidata 3.1, will be used for data entry. Two people will perform data entry independently, and they will be trained in advance and pass a test before they begin the work. The data will then be transferred to Statistical Package for the Social Sciences (SPSS) software for data analysisThe statistical analyses were pre-specified and performed on an intention-to-treat (ITT) basis. The ITT analysis will include all patients who were randomly recruited, and the per-protocol (PP) analysis includes patients who completed the study and did not have major protocol violations. All analyses are based on the ITT population, and the result of the ITT analysis is compared with the PP analysis to assess the sensitivity. All missing data are analyzed using the last observation carried forward (LOCF) imputation method. Changes from baseline in outcome measurement among the two groups are analyzed using analysis of variance (ANOVA) or the Kruskal-Wallis test when appropriate. The Bonferroni methods for multi-comparisons are performed if the tests are statistically significant. Safety analysis is analyzed mainly using descriptive statistics. All statistical tests are in a two-tailed t test at a 5% level of significance (Additional file 1).Data will be analyzed by an independent statistician. Data for continuous variables are reported using mean (standard deviation; SD) for normally distributed data or median (range) for skewed data. Data for categorical variables are expressed as number (percentage). Intergroup differences are assessed for significance using Student’s *t* test for normally distributed continuous variables or the Mann-Whitney U test for skewed continuous variables. Intergroup differences in categorical data are assessed using the *χ*^2^ test or Fisher’s exact tests (two-tailed), as appropriate. Length of hospital stay is calculated using Kaplan-Meier analysis to compare differences between groups. Data are analyzed using SPSS 19.0 (IBM, Armonk, NY, USA), with the threshold of significance defined as a two-tailed *p* < 0.05.

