### Participants

Participants who have undergone laparoscopic radical resection of rectal carcinoma in the Gastrointestinal Surgery Department or laparoscopic panhysterectomy of benign lesions in the Gynecology Department of Guangdong Provincial Hospital of Traditional Chinese Medicine will been recruitment. The inclusion, exclusion, and elimination criteria are listed in Table 1.

**Table 1 Tab1:** Inclusion, exclusion, and elimination criteria

Category	Criteria
Inclusion criteria	Patients who have undergone surgery for gastric or colorectal cancer, or hysterectomy for hysteromyoma Age 40–75 years old Duration of surgery, 1–4 h Time under anesthesia, 1.5–4.5 h TCM syndrome, Qi deficiency and Qi stagnation Provision of signed, informed consent
Exclusion criteria	Advanced malignant tumor cachexia, extreme weakness Malignant tumors requiring extended radical surgery Cardiovascular, liver, kidney, brain, or lung co-morbidity, or other serious diseases Poorly controlled hypertension or diabetes Mental disability Allergy to the intervention Pregnant or breast-feeding women Severe malnutrition (serum albumin < 21 g/L, pre-albumin < 0.1 g/L) Repeated abdominal surgery and severe intestinal adhesions Blood loss > 400 mL during surgery Serious complications occurring within 6 h after surgery (e.g., multiple organ dysfunction) Postoperative intraperitoneal hyperthermic perfusion Emergency surgery Prokinetic drugs prescribed after surgery Patient participating in another clinical study, or having participated in another clinical study in the previous month Patient considered inappropriate to participate the study by clinical investigators
Elimination criteria	Do not meet the inclusion criteria, but mistakenly included Worsening condition that cannot be controlled in 3 days Other complications because of interventions, including severe allergy or serious adverse events Serious complications, infection, or requiring a second operation during treatment Refusal to continue the treatment, regardless of the reason

*TCM* traditional Chinese medicine

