### Trial procedure

The entire trial will include a preoperative assessment, an intervention phase (generally 1–7 days), and a 2-month follow-up phase. Included subjects will be randomized to groups receiving XBP or a placebo, using a stratified random system, and acquire a random number (corresponding to numbered drugs) in this phase. Participants will be instructed to take the medicine twice every day after surgery (excluding the surgery day) at 09:00 and 16:00 until defecation occurs. Any remaining medicine will be recovered and recorded. Subjects will be evaluated at least three times per day (between 01:00 and 09:00, 09:00 and 17:00, and 17:00 and 01:00) and the results recorded in a Case Report Form (CRF) until they leave the hospital. The participant flowchart is shown in Fig. 1 and the Standard Protocol Items: Recommendations for Interventional Trials (SPIRIT) Figure for the trial is shown in Fig. 2. Adverse events will be monitored by telephone calls to subjects on the 14th and 60th days after surgery.

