### Intervention

The oral Chinese herbal medicine granule (XBP or placebo) is produced by Guangdong Province Engineering Technology Research Institute of TCM, which holds a Good Manufacturing Practice certificate.

After surgery, all included subjects will be administered conventional therapies, including antibiotics and liquid support. Both groups will receive individually packaged doses of XBP or placebo, with instructions that each dose should be dissolved in warm water and consumed per os twice daily after surgery at 09:00 and 16:00 until defecation occurs.

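### Read literally, the protocol puts safety on everyone randomized, although its dosing window allows randomized patients who never take a dose; the likely dilution is small and the fix is one sentence

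*Protocol article*

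**What the plan says.** All of the population wording is in the protocol article, Data collection and statistical analysis. It defines ITT by randomization alone: "The ITT analysis will include all patients who were randomly recruited". It defines one other set: "the per-protocol (PP) analysis includes patients who completed the study and did not have major protocol violations". It then assigns the first of these across the board: "All analyses are based on the ITT population", with per-protocol kept as a sensitivity comparison. A few sentences later in the same paragraph comes safety: "Safety analysis is analyzed mainly using descriptive statistics". That sentence names no population and states no exception.

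On dosing, Trial procedure tells participants to "take the medicine twice every day after surgery (excluding the surgery day) at 09:00 and 16:00 until defecation occurs". The Intervention section repeats the clock times and the stopping point: "consumed per os twice daily after surgery at 09:00 and 16:00 until defecation occurs". Among the elimination criteria in Table 1 (Participants) are mistaken inclusion, complications caused by the intervention (severe allergy and serious adverse events among them), and "Refusal to continue the treatment, regardless of the reason".

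**The concern.** Analysing everyone as randomized is the cautious choice for efficacy, because patients who take no drug pull the estimated effect towards zero. For harm the same pull works the other way: a patient who took no XBP cannot have a reaction to it, yet adds one to the XBP denominator. The XBP rate falls and the two arms move closer together.

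The trial's own rules make such patients possible. Someone who is randomized and then defecates, withdraws or is found ineligible before the first 09:00 dose on the day after surgery takes nothing.

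The per-protocol set is no remedy. It keeps completers, and patients eliminated for an intervention-related complication or a serious adverse event would not naturally count as completers. Of the two sets defined, one can include people never exposed and the other tends to lose the people who were harmed. Safety is a declared aim of the trial (Abstract; Methods/design), so its denominator should be people exposed to the product.

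**Working it through.** **1. Does the text cover safety?** ITT is everyone randomized; all analyses use ITT; safety is an analysis described in the same paragraph; no exemption is given. Taken at its word, the safety table uses all randomized patients by assigned arm.

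**2. Can a randomized patient have zero doses?** Yes. No dose is given on the day of surgery (Trial procedure), and dosing ends at first defecation (Trial procedure, Intervention). The article does not say how often this would happen, gives no assumed time to first defecation, and is unclear on when randomization takes place.

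**3. Arm size.** The article's own figures (Sample size estimation) are 89 per group and 15% dropout: 89 / (1 − 0.15) = 104.7, rounded up to 105, which matches. The total of 420 equals 4 × 105. The allocation ratio is not stated; assuming 1:1, each arm has 420 / 2 = 210. The 89 itself cannot be checked, because neither an SD nor a power is stated.

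**4. Size of the dilution.** Let n = 210 be the arm size and u the number undosed. Assume a rate of 10% in patients who took XBP, and a background rate of 5% in undosed patients and in the placebo arm, with the same u in both arms.

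- XBP rate over all randomized = (0.10 × (n − u) + 0.05 × u) / n
- Difference between arms = (0.10 − 0.05) × (n − u) / n
- XBP rate if undosed patients have no events, as for drug-caused reactions only = 0.10 × (n − u) / n

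| Undosed share | u | XBP rate | Difference (points) | XBP rate, no events in undosed |
|---|---|---|---|---|
| 0% | 0 | 10.00% | 5.00 | 10.00% |
| 1% | 2 | 9.95% | 4.95 | 9.90% |
| 5% | 10 | 9.76% | 4.76 | 9.52% |
| 10% | 21 | 9.50% | 4.50 | 9.00% |
| 15% | 32 | 9.24% | 4.24 | 8.48% |

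Example, 5% row: (0.10 × 200 + 0.05 × 10) / 210 = 20.5 / 210 = 9.76%.

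**5. Against sampling error.** The standard error of a 10% rate in 210 patients is √(0.10 × 0.90 / 210) = 2.07 points. The shifts at 1% and 5% undosed, 0.05 and 0.24 points, are about 2% and 12% of one standard error.

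**6. A loose ceiling on the defecation route.** No undosed share is documented, but first flatus gives a bound. A difference of 4.72 h, 89 per group and two-sided 5% imply SD = 4.72 × √(89/2) / (z for alpha + z for power) = 11.24 h at 80% power or 9.71 h at 90%; the power is my assumption. Take the placebo mean of 26.78 h, normal times, and a first dose 15 to 21 h after surgery (surgery ending between 18:00 and 12:00). The share with flatus before the first dose then runs from Φ((15 − 26.78)/9.71) = 11% to Φ((21 − 26.78)/11.24) = 30%. If defecation comes no earlier than flatus, and usually later, the share undosed by this route should be well below those figures.

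**The case against.** The strongest reply is that the safety population is inferred from one word. The sentence about the ITT population goes on to the per-protocol comparison and is followed by missing data and changes from baseline, so its setting is efficacy. The safety sentence names no set, and Additional file 1, cited right after it, is not shown. A condensed article may leave a safety set to a fuller document. This has weight: a missing safety set would not be a finding. But the article does state a population for all analyses; if a fuller document defines a safety set, this sentence conflicts with it and still needs narrowing.

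Three stronger readings are tempting and do not hold.

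- *A reader might infer that the dosing rules do leave patients undosed.* They only permit it. Eligibility depends on blood loss during surgery and on complications up to 6 h afterwards (Table 1), so if randomization follows eligibility the window before the first dose is short. The Background puts colonic recovery at 48–72 h, and first flatus is assumed at 26.78 h on placebo. The refusal criterion speaks of continuing treatment, which mainly describes patients already dosed.
- *A reader might take the 15% dropout as the undosed share or its upper limit.* Dropout covers any loss after randomization, and nothing links the two. The 10% and 15% rows above show how the formula behaves; they are not expectations.
- *A reader might conclude that the safety results will be materially diluted.* The Safety assessment section records all adverse events, and undosed surgical patients still have background events. At small undosed shares the shift is a fraction of a percentage point, far inside sampling error.

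It is also fair to say that no route to receiving the wrong product is described, so grouping by product taken is a convention here rather than an answer to a known problem.

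**Conclusion.** The point holds as a minor one. The stated rule literally places safety on everyone randomized, the dosing window allows patients with no dose, and counting them biases harm towards no difference. The size cannot be derived from the article, because the undosed share is not given. With 1% to 5% undosed, the XBP rate would read 9.95% to 9.76% instead of 10%, and the difference between arms 4.95 to 4.76 points instead of 5. These figures rest on assumed rates of 10% and 5%, 1:1 allocation, and equal undosed shares in both arms. A shift of that size would be unlikely to change the reading of a descriptive safety table. The reasons to act are that the error runs in the unsafe direction and that correcting it costs almost nothing.

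**What to change.** In Data collection and statistical analysis:

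1. Limit the ITT statement to the efficacy analyses, leaving those unchanged.
2. State that safety is analysed in all patients who took at least one dose of study medicine, grouped by the product actually taken and regardless of later elimination.
3. Report, for each arm, the number randomized but never dosed.

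Doses taken can be read from the record of recovered medicine already planned under Trial procedure and Quality control, so no new data are needed. The article reports recruitment as ongoing and the codes as blinded until all processes are completed, apart from stated exceptions, so the change can still be made in advance of unblinded results. The only downside is a slightly smaller safety denominator. If Additional file 1 or an analysis plan already defines such a set, align the article's sentence with it.

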### Outcome measures

1. Primary outcome measures: time to first flatus, time to first defecation, time to first bowel sounds, time to consuming liquid/semi-liquid/general diet

2. Secondary outcome measures: gastrointestinal symptoms, such as abdominal distention and pain, nausea, vomiting; serum hormone levels, including ghrelin, motilin, corticotropin-releasing hormone, and bradykinin; electrogastrogram

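### Agreement between LOCF-based ITT and a completer per-protocol set is not adequate evidence of robustness if slow recoverers leave unequally by arm

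*Protocol article*

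**What the plan says.** The relevant text is in the protocol article, Data collection and statistical analysis.

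- ITT set: "The ITT analysis will include all patients who were randomly recruited".
- Missing data: "All missing data are analyzed using the last observation carried forward (LOCF) imputation method".
- PP set: "the per-protocol (PP) analysis includes patients who completed the study and did not have major protocol violations".
- Robustness check: "the result of the ITT analysis is compared with the PP analysis to assess the sensitivity".

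The Outcome measures section lists the endpoints: "Primary outcome measures: time to first flatus, time to first defecation, time to first bowel sounds, time to consuming liquid/semi-liquid/general diet". All are first-event times, observed in hospital. The Trial procedure section describes the trial as a preoperative assessment followed by "an intervention phase (generally 1–7 days), and a 2-month follow-up phase", and gives the day-14 and day-60 telephone calls to adverse-event monitoring. Table 1 eliminates patients for uncontrolled deterioration, serious complications, infection, reoperation, or declining further treatment. Sample size estimation allows for 15% dropout. The article does not say what event marks completion of the study.

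**The concern.** A sensitivity analysis for missing data should change the assumption about the patients whose data are missing. The two analyses compared here may not do that in the direction that matters.

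Take a patient who leaves before first flatus or defecation. LOCF has no natural value for an event that has not happened. The obvious reading is the last time seen, which is earlier than the true event time. The PP set drops the same patient. Neither analysis counts the patient as a late recoverer.

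Several elimination reasons in Table 1 plausibly go with slow recovery, and some, such as complications of the intervention, could differ by arm. If so, ITT and PP share the direction of bias, and their agreement could be reported as robustness when both are wrong.

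A second, smaller issue is that completion is not tied to the in-hospital phase. The wording therefore leaves room to exclude from PP a patient whose primary times are all known.

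**Working it through.** **Inputs from the article.** Mean time to first flatus 22.06 h (XBP) and 26.78 h (placebo), difference 4.72 h; 89 per group before dropout; 15% dropout; two-sided 5% level.

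**The plan's own figure.** 89 / (1 − 0.15) = 104.7, rounded up to 105 per group, as stated. The total of 420 is 4 × 105.

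**Standard deviation (not stated, so implied).** SD = 4.72 × √(89/2) / (z for alpha + z for power).
- 80% power: 4.72 × 6.671 / (1.960 + 0.842) = 11.24 h.
- 90% power: 4.72 × 6.671 / (1.960 + 1.282) = 9.71 h.

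**Check 1: bias in hours with no true effect.** Assumptions: gamma times, mean 26.78 h, SD 11.24 h; 400,000 patients per arm; leavers last seen at a uniform fraction of their true time; LOCF equals that time. Bias is placebo minus XBP, so a positive value favours XBP.

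| Loss pattern | XBP vs placebo loss | LOCF-ITT | PP |
|---|---|---|---|
| Rises with recovery time | 20% vs 10% | +1.65 | +0.86 |
| Rises with recovery time | 25% vs 5% | +3.31 | +1.75 |
| Rises with recovery time | 10% vs 20% | −1.62 | −0.84 |
| Random | 20% vs 10% | +1.36 | about 0 |
| Random | 25% vs 5% | +2.67 | about 0 |
| Either | 15% vs 15% | about 0 | about 0 |

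The random rows can be checked by hand. A leaver's time is halved on average, so the expected bias is 0.5 × 26.78 × (0.20 − 0.10) = 1.34 h, close to the simulated 1.36 h. In the first row, the biases are 1.65/4.72 = 35% and 0.86/4.72 = 18% of the planned difference.

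**Check 2: false claims for XBP with no true effect (nominal 2.5%).** Assumptions: 105 per arm; lognormal times, mean 26.78 h, SD 11.2 h; 5% random loss per arm, plus an extra share of the XBP arm taken from its slowest third; leavers' ITT value 30–95% of the true time; Mann-Whitney test.
- Extra 5%: ITT 7.6%, PP 6.6%.
- Extra 10%: ITT 16.7%, PP 15.3%.
- Random loss of 15% vs 5%, no extra: ITT about 10%, PP 2.6%. PP confirms only 22% of the false ITT claims.

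Repeat runs gave about 6–8% and 15–17% for ITT, and 6–7% and 13–15% for PP, in the first two scenarios.

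**Check 3: does worst rank solve it?** This ranks patients without an observed event after all observed times. In the two extra-loss scenarios above it gives false XBP claims of 1.3% and 0.5%. Under random 15% vs 5% loss it falsely shows XBP worse in 25% of null trials. If the extra 10% of slow leavers are in the placebo arm, it falsely favours XBP in 5.4%. It is a bound and is not conservative in general.

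**The case against.** The strongest reply is that ITT against PP is a conventional comparison and does work in some settings. That stands. When loss is unequal but unrelated to recovery, PP is about unbiased, LOCF-ITT is not, and the two diverge visibly. A reader might infer that agreement between them shows nothing; the calculations do not support that. PP also probes the effect of protocol violations.

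It also stands that a high rate of PP confirming false ITT claims proves little. With no informative loss at all, PP confirms about 70% of chance ITT findings, because the two sets share most patients.

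The direction is not fixed by the text either. LOCF for a first-event time is undefined in the article, and extra slow leavers on placebo would bias both analyses against XBP. The three-day deterioration criterion would seldom precede first flatus: under the lognormal model only 0.4% of times exceed 72 h. The other elimination reasons carry no such delay, however, and the later primary events, such as defecation and general diet, were not simulated.

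A reader might infer that a missed day-60 call removes a patient from PP. No sentence says so. It is one literal reading of an undefined term, and the Discussion places the main phase in hospital. Nor does a power loss follow: cutting 89 to 80 per group needs an assumed 10% loss beyond the 15% already allowed, and the main analyses are on ITT.

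Finally, further sensitivity analyses may sit in the additional file or a separate analysis plan, neither of which is shown.

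**Conclusion.** The point holds in a conditional form. If patients who leave before the event are mostly slow recoverers, are lost unequally by arm, and are assigned the last time seen, then ITT and PP are biased in the same direction and their agreement is not adequate evidence of robustness. For a 20% vs 10% split, the spurious difference is 1.65 h (ITT) and 0.86 h (PP) out of a planned 4.72 h. In the test-based model, false XBP claims rise from 2.5% to about 7–17% in both analyses.

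The loss splits, SD, distributions and LOCF reading are assumptions. With equal loss and no true effect the problem disappears, and with random unequal loss the comparison is informative. The undefined completion criterion is a point for clarification and not a stated exclusion rule. The finding concerns what the article fixes as its check and does not claim that no other sensitivity analysis exists.

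**What to change.** In Data collection and statistical analysis, keep the ITT-PP comparison as a supplement and add two sensitivity analyses on all randomized patients:

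1. A time-to-event analysis (stratified log-rank or Cox) that censors patients without an observed event when last seen. This still assumes that leaving is unrelated to recovery time, so it should not stand alone.
2. A worst-rank analysis, with patients lacking an observed event ranked after every observed time. Report it as a bound and not as the sole criterion for calling the result robust.

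Define completion for PP by the in-hospital phase in which the primary times are observed, so that a missed day-14 or day-60 adverse-event call cannot remove a patient.

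The cost is a wording change and some extra analysis, with no new data beyond the time each patient was last assessed, which the daily assessments should already supply. The worst-rank bound can look unfavourable to whichever arm loses more patients, and the report should say so.

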### Sample size estimation

The study consists of two groups: the sample size estimation was based on our previous prospective clinical study performed in patients who underwent gynecologic transabdominal surgery [1]. Time to first flatus was assumed to be 22.06 and 26.78 h between the XiangBin granules and the placebo groups, respectively. The minimum detectable difference, 4.72 h, was used to estimate the value of the overall parameters. PEMS 3.1 Software for Windows was used to randomly assign the patients to the treatment or the placebo group. The rounded sample size for each group was 89. Assuming a 15% dropout rate, the final sample size would be 105 for each group. Therefore, 420 participants who have undergone laparoscopic radical resection of rectal carcinoma and laparoscopic panhysterectomy of benign lesions will been recruited.

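### LOCF is prescribed for all missing data, but for the primary time-to-first-event outcomes it is either undefined or, if the last-seen time is entered, biased towards early recovery

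*Protocol article*

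**What the plan says.** The section on data collection and statistical analysis gives one missing-data rule for the whole trial: "All missing data are analyzed using the last observation carried forward (LOCF) imputation method". The outcome section lists "Primary outcome measures: time to first flatus, time to first defecation, time to first bowel sounds, time to consuming liquid/semi-liquid/general diet". All of these are waiting times to a first occurrence.

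The same analysis section keeps every randomised patient in the main analysis: "All analyses are based on the ITT population, and the result of the ITT analysis is compared with the PP analysis to assess the sensitivity". Continuous outcomes are compared by Student's t test "or the Mann-Whitney U test for skewed continuous variables". Kaplan-Meier appears once, for a quantity that is not among the listed primary or secondary outcomes: "Length of hospital stay is calculated using Kaplan-Meier analysis to compare differences between groups".

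On observation, the trial procedure says "Subjects will be evaluated at least three times per day", with "the results recorded in a Case Report Form (CRF) until they leave the hospital". Table 1 lists grounds for elimination that can arise before bowel function returns: uncontrolled worsening, serious complications or infection, a second operation, and refusal of further treatment. The sample size section allows for loss: "Assuming a 15% dropout rate, the final sample size would be 105 for each group".

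**The concern.** LOCF presupposes a series of measurements of the same quantity. A time to first flatus, defecation, bowel sounds or diet is not a series. Until the event happens, the record says only that it has not happened yet. A patient who leaves observation at time t is known to have a waiting time longer than t, which is a right-censored value.

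The ITT set and the tests named for continuous data require a number for every patient. The number nearest to hand is t itself. Entering it replaces a waiting time longer than t by one equal to t, which is always too short.

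The patients affected are unlikely to be a random subset, since worsening, complications and reoperation plausibly go with slow recovery. If one arm loses more patients before the event than the other, that arm looks faster for a reason unrelated to the treatment.

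**Working it through.** **Inputs from the protocol article (sample size and analysis sections).** Mean time to first flatus 22.06 h (XBP) and 26.78 h (placebo); difference 4.72 h; 89 per group before dropout; 15% dropout; 105 per group; 420 in total; two-sided 5% level.

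**The plan's own figure.** 89 / (1 − 0.15) = 104.7, rounded up to 105 per group. This reproduces. The total of 420 with two arms would be 210 per arm, so both sizes are used below.

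**Assumed SD.** The article states neither SD nor power. Inverting the two-means formula, SD = 4.72 × √(89/2) / (1.96 + z_power):
- 80% power: 4.72 × 6.671 / 2.802 = 11.24 h
- 90% power: 4.72 × 6.671 / 3.242 = 9.71 h

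**Assumed loss model.** A fraction q of an arm is lost before the event, at a point uniform over the patient's own waiting time T, and the last-seen time is entered as the event time. With mean m and SD s of the true times:
- mean entered = m(1 − q/2)
- variance entered = (m² + s²)(1 − 2q/3) − [m(1 − q/2)]²

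**No true effect, m = 26.78 h, s = 11.24 h, loss 20% on XBP and 10% on placebo.**
- Means entered: 26.78 × 0.90 = 24.10 h and 26.78 × 0.95 = 25.44 h; false difference 1.34 h in favour of XBP.
- Variances entered: 150.1 and 140.0.
- At 105 per group: SE = √(290.2/105) = 1.66 h, ratio 1.34/1.66 = 0.81, two-sided rejection about 13%.
- At 210 per group: SE = √(290.2/210) = 1.18 h, ratio 1.14, rejection about 21%.

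The same steps for other loss patterns (s = 11.24 h):

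| Loss, XBP vs placebo | False difference | Type I error, 105 per group | Type I error, 210 per group |
|---|---|---|---|
| 15% vs 15% | 0 h | 5% | 5% |
| 4% vs 2% | 0.27 h | about 5% | about 6% |
| 20% vs 10% | 1.34 h | about 13% | about 21% |
| 25% vs 5% | 2.68 h | about 37% | about 63% |

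Simulation with lognormal times agrees (about 13% and 36-38% at 105 per group; 20-21% and 61-64% at 210). With s = 9.71 h, the 20% vs 10% error at 105 per group is about 15%.

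**True effect of 4.72 h.**
- 15% loss in each arm: 4.72 × 0.925 = 4.37 h, a mild dilution.
- 10% on XBP, 20% on placebo: 26.78 × 0.90 − 22.06 × 0.95 = 3.1 h. Power at 105 per group is then 48-57%, against 86-94% with complete data (SD 11.24 to 9.71 h).
- 20% on XBP, 10% on placebo: 26.78 × 0.95 − 22.06 × 0.90 = 5.6 h.

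**Does the planned sensitivity analysis help?** The per-protocol set is limited to patients who completed the study without major violations. It therefore removes many of the patients with missing event times, and agreement between the two analyses would not show that their handling was harmless.

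**The case against.** The strongest counter-argument is that little may be missing. Patients are assessed at least three times a day in hospital, the planning times for flatus are 22 to 27 h, and stopping the study product need not stop assessment. Loss before flatus could then be a few per cent, and at 4% vs 2% the harm is negligible. This stands for flatus. It is weaker for defecation and general diet, which are more exposed to withdrawal or discharge before the event.

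Two stronger readings are tempting and not supported. A reader might infer that the plan scores a patient lost before the event as recovered when last seen. The article does not say so. It does not explain how LOCF is turned into an event time, and that reading is an inference from the need to give the named tests a number. A reader might also infer that 15% of patients are expected to be censored. The 15% is a general dropout allowance in a trial with a two-month follow-up, and loss after the event cannot affect these outcomes. It is an upper bound on the average pre-event loss the plan allows for.

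The uniform-loss model also does not fit every route out. A patient eliminated for worsening that stays uncontrolled over 3 days may be last seen near or beyond 72 h. The value entered would be long compared with a 26.78 h mean, though still shorter than the true time, so such a patient would not make the arm look fast on flatus.

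None of this makes LOCF a workable rule for these outcomes.

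**Conclusion.** The rule is wrong as written for the primary outcomes. Either it cannot be carried out, or it turns censored times into early events. That conclusion needs no numerical assumption; it follows from the all-inclusive LOCF sentence, the list of primary outcomes, and the ITT analysis with tests that do not handle censoring.

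The size is uncertain. It depends on the SD, on when patients are lost, on the imbalance between arms and on all the loss preceding the event, none of which the document gives. The larger error rates in the table need a two-fold or five-fold imbalance in pre-event loss and should be read as unfavourable scenarios, not as forecasts. High confidence belongs to the unsuitability of the rule, not to any particular figure.

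**What to change.** Before unblinding:

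1. Remove LOCF for the time-to-event outcomes. Right-censor each patient without the event at the last assessment at which it had not occurred.
2. Specify Kaplan-Meier curves with a log-rank test (or Cox model), stratified by the randomisation strata, as the primary analysis of these outcomes in place of the t test or Mann-Whitney test. The plan has no such analysis for them now, so it must be written in, with the strata named.
3. Add a required sensitivity analysis that assigns the longest time to patients withdrawn for worsening or complications. Their censoring is informative, so plain censoring alone is not enough.
4. Confine any imputation rule to the serially measured secondary outcomes.

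The cost is a change of primary test, which is more than a wording edit. No new data are needed, since the assessments made at least three times daily are already recorded in the CRF.
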